## Abstract

**Background:**

Distressing nightmares are a core symptom of posttraumatic stress disorder (PTSD) and contribute to psychiatric comorbidity, impaired physical health and decreased social functioning. No specific pharmacological treatment for PTSD-related nightmares is yet approved. Preliminary clinical data indicate that cannabinoid agonists can improve nightmares and overall PTSD symptoms in patients with PTSD. The primary objective of the study is to examine the efficacy of oral dronabinol (BX-1) versus placebo in reducing nightmares in patients with PTSD. The secondary objectives of the study are to examine the efficacy of oral BX-1 in reducing other PTSD symptoms.

**Methods:**

The study is designed as a multi-centric, double-blind, randomized (1:1), placebo-controlled, parallel group interventional trial. Eligible patients will be randomized to BX-1 or placebo, receiving a once-daily oral dose before bedtime for 10 weeks. Primary efficacy endpoint is the Clinician-Administered PTSD Scale (CAPS-IV) B2 score for the last week, measuring frequency and intensity of nightmares. Secondary efficacy endpoints are other disorder-specific symptoms in patients with PTSD. Further, tolerability and safety of dronabinol will be assessed.

**Discussion:**

This randomized controlled trial will provide evidence whether treating patients with PTSD and nightmares with dronabinol is safe and efficacious.

**Trial registration:**

NCT04448808, EudraCT 2019–002211-25.

**Supplementary Information:**

The online version contains supplementary material available at 10.1186/s12888-023-04818-5.

## Background and rational

Posttraumatic stress disorder (PTSD) is associated with serious disability, medical illness, and a severely impaired quality of life [14, 20]. The WHO has reported an overall disability-adjusted life year (DALY) rate per 100,000 inhabitants of Germany of 54 for PTSD; 80 in women, 28 in men [22]. PTSD places a high socioeconomic burden on patients with marked reductions in household income [19]. More than 50% of patients with PTSD suffer from comorbid mood, anxiety, and substance-use disorders [16]. Various medical comorbidities are very common in PTSD patients with cardiovascular diseases among the most prevalent [15]. Nightmares also contribute to alcohol and substance abuse, suicidal ideation, and even completed suicide [17]. Further, distress related to insomnia is one of the most common residual symptoms after specific psychotherapy for PTSD [13]. Only selective serotonin reuptake inhibitors (SSRIs; in Germany and FDA: paroxetine and sertraline) are currently approved as pharmacological treatment for PTSD with low response and remission rates [10] and there is no evidence that SSRIs have an effect on nightmares in PTSD [7].

Accumulating clinical data indicate that cannabinoid agonists (e.g., dronabinol) can improve nightmares and overall PTSD symptoms in patients with PTSD [23]. First, many patients with PTSD cite motives of self-medication for continued use of cannabis due to its ability to promote relaxation and sleep, and reduce anxiety symptoms and hyperarousal [2, 5, 6]. Second, an uncontrolled open-label study of nabilone (0.5-6 mg/day) at bedtime reduced nightmares in patients with PTSD, 34 out of 47 patients exhibiting either total cessation or significant reduction in nightmares [11]. Third, a retrospective chart review showed that nabilone (mean dose 4 mg/day) treatment was associated with a significant improvement in sleep and a reduction in nightmares (severity and frequency) as well as a general reduction in PTSD symptom severity [8]. Fourth, an open label, uncontrolled pilot study examined the impact of adding 5 mg of Δ(9)-THC twice a day as add-on treatment onto existing medications in patients with PTSD and found that THC consumption specifically improved sleep quality, reduced nightmares, and reduced symptoms of hyperarousal [18]. Fifths, a small, randomized, double-blind, placebo controlled crossover study assessed nabilone (3 mg daily) and found significant reduction in severity and frequency of nightmares, and increased general well-being [12]. After approval of the first version of this study protocol (version 1.1), results of a randomized trial on smoked cannabis preparations versus placebo on symptoms in patients with PTSD was published [4]. Results revealed no significant difference in change in PTSD symptom severity between the active cannabis concentrations and placebo. However, the small sample size (*N* = 20 per group) and short observation period (3 weeks) restrict the interpretation of the findings. Nevertheless, based on these findings, the sponsor of the current study decided to implement an initially unplanned interim analysis (see statistical analysis plan for interim analysis in the supplements, description in the manuscript and in protocol version 2.0).

### Objectives

The primary objective of the study is to examine the efficacy of oral BX-1 over placebo in reducing nightmares in patients with PTSD. The secondary objectives of the study are to examine the efficacy of oral BX-1 in reducing other PTSD-specific symptoms.

### Trial design

The THC-PTSD-Study is designed as a multi-centric, double-blind, randomized (1:1), placebo-controlled, parallel group interventional exploratory phase II trial.

## Methods

The protocol follows the Standard Protocol Items: Recommendations for Interventional Trials (SPIRIT) 2013 statement [9]. Corresponding sections are outlined in the SPIRIT checklist (see Supplement).

### Study sample and setting

One hundred seventy-six patients with nightmares and PTSD will be enrolled in the study (but see above for interim analysis). Participants will be allocated to two treatment arms: oral dronabinol (BX-1) or placebo (see Fig. 1).

**Fig. 1 Fig1:**
[figure not shown]
Treatment schedule

The study will be conducted at three university hospitals in Germany which provide specialized PTSD treatment services: The Department of Psychiatry and Neuroscience at Charité – Universitätsmedizin Berlin, Campus Benjamin Franklin, the Department of Psychiatry and Neuroscience, Charité – Universitätsmedizin Berlin at St. Hedwig Hospital, and the Department of Psychosomatic Medicine and Psychotherapy, Central Institute of Mental Health Mannheim.

### Eligibility criteria

Patients must provide written, informed consent before any study procedures occur (see supplements for Informed Consent Form). Patients eligible for the trial must comply with the inclusion criteria (see Table 1) at randomization. Exclusion criteria are listed in Table 1.

**Table 1 Tab1:** In- and exclusion criteria of the THC-PTSD-trial

Inclusion criteria	Exclusion criteria
1. Diagnosis of posttraumatic stress disorder (PTSD) according to DSM-5 with a 20 item CAPS-5 total score ≥ 26	1. Lifetime cannabis use disorder
2. At least two nightmares a week, an intensity score ≥ 2, with a CAPS-IV B2 (frequency and intensity for the last week) score ≥ 5	2. Current substance/alcohol use disorder (≤ 3 months)
3. Men and women between 18 and 65 years of age	3. Acute suicidality
4. Written informed consent	4. Psychotic disorder
5. The patient has the capacity to give consent (He/she is able to understand the nature and anticipated effects/side effects of the proposed medical intervention)	5. Bipolar disorder
6. The patient is not breastfeeding	6. Current anorexia nervosa
7. Women of child-bearing potential must have a negative urine or serum pregnancy test	7. Current major depressive episodes and a MADRS score > 29
8. All participants must use highly effective contraception	8. Dementia
9. The patient received stable pharmacological medication for at least 4 weeks prior to study entry (any changes in medication dose or frequency of therapy must be answered with no)	9. Trauma-focused psychotherapy four weeks before the trial
	10. Initiation of sleep medication 4 weeks prior screening or initiation of alpha adrenergic agents 4 weeks prior to screening
	11. Acute or unstable medical illness
	12. Epilepsy
	13. Relevant heart diseases
	14. Known HIV- and/or active Hepatitis-B- or Hepatitis-C-infection
	15. Current or past malignant illness
	16. The patient is unwilling to consent to saving, processing and propagation of pseudonymized medical data for study reasons
	17. Patients, who may be dependent on the sponsor, the investigator or the trial sites, have to be excluded from the trial
	18. The patient is legally detained in an official institution
	19. The patient does have a known allergy or contraindication against Dronabinol
	20. The patient does have clinically significant abnormalities in 12-lead ECG
	21. The patient does have clinically significant laboratory abnormalities
	22. The patient did participate in other interventional trials during the 3 months before and at the time of this trial

*CAPS-5* Clinician-Administered PTSD Scale for DSM-5 (last month version), *CAPS-IV B2* B2 score of the Clinician-Administered PTSD Scale for DSM-IV (frequency and intensity of nightmares), *MADRS* Montgomery–Åsberg Depression Rating Scale, *HIV* Human immunodeficiency virus, *ECG* Electrocardiogram

### Interventions

Eligible patients will be randomised in equal proportions to dronabinol (BX-1) and placebo, receiving a once-daily oral dose before bedtime for 10 weeks. Of these 10-weeks, the first 4 weeks are considered the titration period, the following 6 weeks are the maintenance period with stable dose.

BX-1 is an oily solution containing 25 mg/ml dronabinol. Dronabinol ((-) trans-Δ9-Tetra-hydrocannabinol, Δ9-THC) is the major psychoactive constituent of Cannabis sativa L.. Dronabinol is a clear to amber resin. It is highly lipid-soluble, thermolabile, photolabile and susceptible to oxidation. There is no discernible difference between BX-1 and the corresponding placebo with regard to color, taste, and appearance, thus ensuring the trial`s double-blind character. BX-1 and placebo are filled in bottles. Study medication (IMP) and placebo will be provided by Bionorica SE, Neumarkt, Germany.

### Titration period

The titration period lasts 4 weeks and is performed double-blinded, neither the patient nor the investigator/sponsor knows the identity of the IMP.

All patients in the active treatment group start with 2.5 mg BX-1 and keep the dose constant for 4 days. On the following day (day 5), an increase with additional 2.5 mg BX-1 (5 mg BX-1 total dose) can be done. This increase with additional 2.5 mg BX-1 can be repeated on day 8, day 12, day 15 and day 19 (Fig. 1). However, 15 mg BX-1 as the maximum dose per day is not the treatment goal of this trial, but patients are instructed to define the optimal dose together with the study personnel. The optimal dose is reached if nightmares are eliminated completely. Patients in the placebo condition receive an equal amount of undistinguishable placebo.

### Maintenance period

The individually established daily dose at day 28, will be maintained throughout the 6 weeks double-blinded maintenance and treatment period (Fig. 1).

### End-of study and safety follow-up

End-of-study is after 10 weeks of intervention (visit 8). No wash-out phase will be performed. Two weeks after end-of-study a safety follow-up will be performed (week 12, visit 9) (Fig. 1). No primary or secondary outcome will be assessed at safety follow-up.

### Modifications

Any modification of the dose of study medication during the trial other than described for the titration and maintenance period will be considered as protocol deviation. Participants have the right to withdraw from the study at any time and for any reason without sanction, penalty, or loss of benefits to which the subject is otherwise entitled. The investigator may decide to withdraw a subject from the study at any time with a reasonable rationale.

### Adherence

Face-to-face adherence reminders will take place at the initial product-dispensing visit and each study visit thereafter. Compliance will be checked for each patient at Visits 2–8 by weighing the bottles when returned by the patient with a calibrated balance. The compliance of the patient will be calculated for each visit and for the complete trial. Patients will be defined non-compliant for the complete trial if less than 80% or more than 120% of the individually established dose (Visit 5) was taken.

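### The whole-trial compliance rule uses the Visit 5 dose as its reference although lower doses are prescribed in titration, so its effective limits depend on the titration path

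*Protocol article*

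**What the plan says.** All of this is in the protocol article.

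- **Adherence.** Bottles are weighed on return at Visits 2 to 8, and compliance is worked out both per visit and over the whole trial. Over the whole trial, a patient counts as failing the rule "if less than 80% or more than 120% of the individually established dose (Visit 5) was taken".
- **Interventions.** The treatment phase has two parts: "the first 4 weeks are considered the titration period, the following 6 weeks are the maintenance period with stable dose".
- **Titration period.** Patients on active drug begin at 2.5 mg on days 1 to 4, and a first optional step to 5 mg is allowed on day 5. Later steps are also optional: "This increase with additional 2.5 mg BX-1 can be repeated on day 8, day 12, day 15 and day 19". The ceiling is 15 mg, which the section says is not a target. Placebo patients take matching volumes, so the same arithmetic applies to them.
- **Maintenance period.** "The individually established daily dose at day 28, will be maintained throughout the 6 weeks".
- **Analysis population and missing data.** The confirmatory analysis uses the full analysis set. The per-protocol set excludes major protocol violations; the article does not say whether non-compliance is one.

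**The concern.** The numerator (bottle weight over Visits 2 to 8) covers titration and maintenance. The reference dose is the one reached only at the end of titration. For an up-titrated patient, some of the first 28 days are therefore judged against a dose not yet prescribed. The 80% and 120% limits then no longer mean 80% and 120% of what the patient was told to take, and their real meaning varies from patient to patient.

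The path is itself a response to treatment. The Titration period section ties the optimal dose to elimination of nightmares, and the section on the rationale for dose selection adds side effects. If dronabinol affects either, paths may differ by arm, and with them the effective strictness of the compliance flag. At stake are the description of adherence and, if the flag feeds the per-protocol set, one sensitivity analysis.

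**Working it through.** **Check of the schedule.** Starting dose plus five steps: 2.5 + 5 × 2.5 = 15 mg, which matches the stated maximum. The article gives no expected compliance percentage to reproduce.

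**Inputs.** 28 titration days and 42 maintenance days, 70 in all (Interventions); permitted step days 5, 8, 12, 15 and 19 (Titration period); Visit 5 dose held to the end (Maintenance period); limits 80% and 120% (Adherence).

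**Formulas**, reading the rule literally over 70 days:

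- Score of a patient who takes every dose: R = (sum of daily prescribed doses) / (70 × Visit 5 dose).
- Share of prescribed drug needed to pass: 0.80 / R.
- Share of prescribed drug tolerated before being flagged for over-use: 1.20 / R.

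**Prescribed totals for selected paths (mg)**

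- No step: 70 × 2.5 = 175.
- Step on day 5 only: 4 × 2.5 + 66 × 5 = 340.
- Step on day 19 only: 18 × 2.5 + 52 × 5 = 305.
- Steps on days 12, 15 and 19: 11 × 2.5 + 3 × 5 + 4 × 7.5 + 52 × 10 = 592.5.
- All five steps: 4 × 2.5 + 3 × 5 + 4 × 7.5 + 3 × 10 + 4 × 12.5 + 10 × 15 + 42 × 15 = 915.

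| Step days | Visit 5 dose | Prescribed | 70 × Visit 5 dose | R | Needed to pass | Over-use limit |
|---|---|---|---|---|---|---|
| none | 2.5 mg | 175 | 175 | 100% | 80.0% | 120.0% |
| 5 | 5 mg | 340 | 350 | 97.1% | 82.4% | 123.5% |
| 19 | 5 mg | 305 | 350 | 87.1% | 91.8% | 137.7% |
| 12, 15, 19 | 10 mg | 592.5 | 700 | 84.6% | 94.5% | 141.8% |
| 5, 8, 12, 15, 19 | 15 mg | 915 | 1050 | 87.1% | 91.8% | 137.7% |

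**All paths.** Five optional steps give 2^5 = 32 patterns. R ranges from 84.6% (steps on days 12, 15 and 19) to 100% (no step). None is below 80% or above 120%. With Visit 8 three days early (67 days, the edge of the visit window in Table 2) the minimum is 84.0%.

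**Same behaviour, different label.** A patient who takes 90% of prescribed drug scores 90% at a constant 2.5 mg (compliant) but 0.90 × 87.1% = 78.4% on the 15 mg path (non-compliant). A patient who takes 130% scores 130% at 2.5 mg (flagged) but 1.30 × 87.1% = 113.3% on the 15 mg path (not flagged).

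**Early stoppers.** A patient who stops before Visit 5 has no established dose to compare with. For later stoppers, assume that only days on drug count. A fully adherent patient on the 15 mg path who stops at day 42 scores 495 / 630 = 78.6% (lowest over all paths 74.4%). From day 54 on, no path falls below 80%. The article does not say how such patients are counted.

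**After the change.** With the cumulative prescribed dose as denominator, R = 100% on every path and the limits are 80% and 120% for everyone. The same holds if the Visit 5 dose is applied to the 42 maintenance days only (on the 15 mg path, 630 / 630).

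**The case against.** The strongest reply is that the article gives no formula. The rule's reference to an individually established dose echoes the Maintenance period section, so it may have been meant for the 42 maintenance days, where the problem disappears. The article does not settle this. But the rule is stated for the complete trial, and the weighings begin at Visit 2, in titration. If only maintenance was meant, the sentence says something else and still needs correcting.

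Several stronger readings are tempting, and the article does not support them:

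- *Fully adherent patients are misclassified.* Not among completers under the published schedule: all 32 paths pass.
- *A dose cut in titration pushes adherent patients over 120%.* If 15 mg were reached and the dose cut on day 28, the score would be 92.3% at 12.5 mg, 100% at 10 mg, 112.9% at 7.5 mg, 138.6% at 5 mg and 215.7% at 2.5 mg. The article describes only increases in titration, and its Modifications section treats other dose changes as deviations.
- *The distortion grows with final dose.* Step timing matters too: one step on day 19 to 5 mg gives the same 87.1% as the full path to 15 mg, and the minimum is at 10 mg.
- *The flag biases the comparison between arms.* The article gives no titration paths by arm, and the primary analysis does not use the flag. An arm difference is possible, not shown.

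**Conclusion.** The point holds in a limited form. Read as written, the rule gives limits that depend on the titration path: from 80% to about 94.5% of prescribed drug at the lower end, and from 120% to about 142% at the upper end. Patients whose intake lies in either range are classified inconsistently, and patients who stop before Visit 5 cannot be classified at all. These figures assume 70 treatment days, steps only on the listed days and the Visit 5 dose applied to every day.

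The primary full-analysis-set result is unaffected. A per-protocol effect requires that non-compliance count as a major violation, which the article does not state; a between-arm effect further requires that paths differ by arm. How many patients would be affected cannot be derived from the article.

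**What to change.** Define compliance as the amount taken, from bottle weight, divided by the sum of the daily doses prescribed over the same days. Calculate it per visit interval and for the whole trial, and apply the 80% and 120% limits to the whole-trial ratio. This also covers patients who stop before Visit 5. Alternatively, if only maintenance was meant, say so and restrict the Visit 5 reference to the 42 maintenance days; patients who stop before Visit 5 then need their own rule.

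The cost is one sentence and a different denominator. The main practical requirement is that the prescribed dose be known for each day. Steps on days 5, 12 and 19 fall between weekly visits, and the article does not say how they are recorded, so the sponsor should confirm that these data exist. No dose or titration rule changes.

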### Pharmacotherapy

All psychotropic medication needs to be stable at least 4 weeks prior to the start of the study (screening) and has to remain stable until visit 8 (end of study). All other non-psychiatric medication has to be stable at least 4 weeks prior to screening and during the entire trial with some exceptions. Medications for minor transient non-psychiatric medical conditions (e.g., common cold and menstrual cramps) such as NSAIDs are allowed. All clinical exacerbation requiring prescription of other psychotropic drugs will be considered a serious adverse event (SAE).

Concomitant pharmacotherapy with Cannabis-based medicine, Cannabis herbs, sleep medication, and alpha-adrenergic agents is not permitted. A more detailed description can be seen in the supplement section.

### Psychotherapy

Non-trauma-focused psychotherapy is allowed if initiated 2 weeks prior to screening and at stable dose during the trial. Psychotherapy frequency has to be documented in the medical file and eCRF. Trauma-focused psychotherapy is not allowed up to 4 weeks prior to the trial (screening) and during the entire trial.

### Outcomes

#### Primary endpoint

The Clinician-Administered PTSD Scale (CAPS-IV) B2 score measuring frequency and intensity of nightmares for the last week, range 0–8 [3] directly after last intervention (10 weeks).

#### Secondary endpoints

Change from baseline of the frequency and intensity of nightmares, measured with the Clinician-Administered PTSD Scale-IV (CAPS-IV) B2 score for the last week, range 0–8, at Visit 3 – Visit 7Change from baseline of the CAPS-5 total score (overall PTSD symptoms, last week) at Visit 6 and Visit 8Change from baseline of the Pittsburgh Sleep Quality Index-Addendum for PTSD (PSQI-A) (PTSD related sleep symptoms) at Visit 2 – Visit 8Change from baseline of the Montgomery-Åsberg Depression Rating Scale (MADRS, depressive symptoms) at Visit 6 and Visit 8Weekly change from baseline of the patients daily total sleep time (in minutes), sleep onset latency at night (in minutes), recuperation of night sleep (5-point Likert scale, 1 = very much; 5 = not at all), and time awake at night (in minutes), number of nightmares last night (0, 1, 3, 4 or more) and intensity of nightmares (5-point Likert scale, 0 = not at all; 5 = extreme) assessed with sleep diaries during Visit 2 – Visit 8Change from baseline of PTSD symptoms assessed with the PTSD Checklist for DSM-5 (PCL-5) at Visit 6 and Visit 8Change from baseline of the Borderline Symptom List 23 (BSL-23) score at Visit 6 and Visit 8Change from baseline of the Health-Related Quality of Life (EQ-5D) score at Visit 6 and Visit 8Overall patients status measured by the Patient Global Impression of Change (PGIC) at Visit 6 and Visit 8Change from baseline of the Social and Occupational Functioning Assessment Scale (SOFAS) at Visit 6 and Visit 8Change from baseline of the Pittsburgh Sleep Quality Index (PSQI) at Visit 6 and Visit 8Change from baseline of symptoms of PTSD and complex PTSD according to ICD-11 assessed with the International Trauma Questionnaire (ITQ) at Visit 6 and Visit 8Change from baseline of THC withdraw symptoms assessed with the Marijuana Withdrawal Checklist (MWC) at Visit 6, Visit 8, and Visit 9Responder analysis: proportion of patients showing improvement in nightmares (change from baseline) defined as decrease of CAPS-IV B2 ≥50% assessed at the end of treatment (Visit 8)Remitter analysis: proportion of patients showing full remission of nightmares defined as CAPS-IV B2 = 0, assessed at the end of treatment (Visit 8)

